### Recruitment of cases and controls

Participants will be recruited during or after their hospital admission or attendance at the ED or MIU. The initial approach to potential participants will be made by clinical staff, followed by contact from researchers where agreement for this is given. Researchers will contact potential participants during their medical attendance, or by telephone or postal invitation within 72 h of ED or MIU attendance. Postal and telephone reminders will be used if no response is received within 2 weeks. Participants will be given a £5 voucher for local stores to thank them for participation in the study.

Controls will be recruited from the community (matched community controls) and from the hospital (unmatched hospital controls). Community controls will be identified from the GP practice where the case is registered, and matched with the case on age (within 4 months) and gender. If the GP practice where the case is registered does not consent to take part, the GP practice closest to the case's GP practice will be asked to recruit controls. GPs or Primary Care Trust staff will invite, by post, parents or guardians (hereafter referred to as parents) of 10 children for each recruited case to take part in the study. One reminder will be sent to non-responders (controls and cases) if they have not replied within 2 weeks of initial mailout. Hospital controls will comprise children already recruited as a case to one of the other ongoing case–control studies, that is, these will be children aged 0–4 years attending the ED or MIU with another injury mechanism (fall on the same level, fall from furniture, staircase fall or poisoning).

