### Definition of exposures and confounding variables

Exposures relating to scalds will be categorised into safety (and other potentially risk reducing) equipment use, safety behaviours and home hazards (see table 1). Cases will be asked about exposures relating to the 24 h (or 1 week for less frequent behaviours) before the scald injury. Controls will be asked about exposures for the 24 h (or 1 week for less frequent behaviours) prior to completing the questionnaire. A range of potential confounding factors will be measured as shown in table 1.

**Table 1 INJURYPREV2014041255TB1:** Definition of exposures and confounding variables

*Exposure: Safety and other potentially risk reducing equipment use* Use of safety gates Kettles with curly or short cables Play pens (or travel cots) Stationary activity centres *Exposure: Safety behaviours* Not drinking hot drinks while holding a child Not passing hot drinks over a child Keeping hot drinks out of reach of children Storing kettles at back of work tops Use of back rings on cooker Turning saucepan handles away from edge of cooker Not using tablecloths Knowledge of hot tap water/thermostat temperature Using cold water first when running a bath Measuring bath water temperature Not leaving child without an adult in the bath or bathroom Not having children running baths Teaching children safety rules about hot liquids *Exposure: Home hazards* Has baby walker	*Potential confounders: sociodemographic* Age Gender Ethnic group Family size and structure Housing tenure Receipt of state-provided means-tested benefits Single parenthood Adult unemployment in the household Overcrowding Deprivation (measured using the Index of Multiple Deprivation^39^) Distance of residence from hospital Use of out-of-home childcare *Potential Confounders**:** child and parent measures for health and behaviour* Child behaviour (infant, early child and child behaviour questionnaires)^40–42^ Child health status (VAS^43^; PedsQL^44^ ^45^) Long-term health conditions Parental mental health (Hospital Anxiety and Depression Scale)^46^ Parenting daily hassles^47^ ^48^ Parental perception of child's ability to reach hot liquids (a series of questions on climbing, reaching, turning on taps, ability to open safety gates)

PedsQL, pediatric quality of life inventory; VAS, visual analogue scale.

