### Analysis

The analysis of the validation of exposures has been described in the falls case–control study protocol.^38^ Relationships between exposures, potential confounding variables and scalds will be explored using causal diagrams. These will be used to identify the minimal set of potential confounding factors to adjust for when estimating ORs. Exposure and confounding variables will be described using frequencies and percentages for categorical variables and means (and SDs) or medians (and IQRs) for continuous variables as appropriate.

Conditional logistic regression will be used for the analysis of cases and matched controls to estimate ORs and 95% CIs, unadjusted and adjusted for confounding variables. All models will a priori adjust for deprivation and distance from hospital. Unconditional logistic regression will be used for the analysis of cases and hospital controls. All models will a priori be adjusted for age, gender, deprivation and distance from hospital, in addition to other potential confounding variables, as described for the matched analysis. Effect modification will be investigated by adding interaction terms to models and where present (p<0.01), stratified results will be reported. Results will also be stratified by the type of service used (child treated in ED or admitted to hospital vs no treatment required) as a proxy for injury severity.

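### The hospital-control models take over an adjustment set that is minimal for scalds, which can leave common causes of an exposure and of the control injury (falls, poisoning) unadjusted

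*Protocol article*

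**What the plan says.** The Analysis section sets one route to the adjustment set. "Relationships between exposures, potential confounding variables and scalds will be explored using causal diagrams", and then: "These will be used to identify the minimal set of potential confounding factors to adjust for when estimating ORs". No other outcome is named for the diagrams.

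For the unconditional models that compare cases with hospital controls, the same section says: "All models will a priori be adjusted for age, gender, deprivation and distance from hospital". Further covariates enter these models by cross-reference: "in addition to other potential confounding variables, as described for the matched analysis".

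Recruitment of cases and controls defines that group: "Hospital controls will comprise children already recruited as a case to one of the other ongoing case–control studies". The mechanisms are "fall on the same level, fall from furniture, staircase fall or poisoning".

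The Abstract presents the hospital controls as an additional group, and the Sample size section is based on the matched comparison only.

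**The concern.** Community controls are meant to represent the population from which the cases arose. For them, a set that closes the paths between exposure and scald is what is needed. Hospital controls are selected by a different injury. The comparison then estimates the scald rate ratio divided by the control-injury rate ratio, given the covariates. It equals the scald effect only if, given those covariates, the exposure is unrelated to falls and poisoning.

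A minimal set makes this harder to satisfy. It drops any covariate that is redundant for scalds, for example one whose link to scalds is already blocked by another covariate. Such a covariate may still influence both the exposure and the control injury.

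At stake is the second set of odds ratios. A null exposure could appear weakly protective or harmful, and part of a difference between the two control groups could come from the adjustment rule. This can also reach kettle, cooker and hot-drink exposures, which have no evident effect on falls or poisoning.

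**Working it through.** **Figures in the plan.** The article gives no figure for this bias. Its only calculation is for the matched analysis: 259 × 4 = 1036 controls, and 1/0.64 = 1.56. Both agree, and neither bears on this point. From it I take only the target odds ratio of 0.64.

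**Structure.** Let E be an exposure, S scald, F the control injury and Z a cause of both E and F. With rare outcomes and covariates C,

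OR(hospital) = RR(E→S | C) / RR(E–F | C).

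If E has no effect on F but Z is not in C, the denominator is not 1.

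**Assumed inputs (none is in the article).** Z has prevalence 0.30 and no effect on scalds given C. Exposure prevalence is 0.40 without Z. The Z–E odds ratio and the Z–F rate ratio are both k.

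**Case k = 2, Z acts on all control injuries, true OR 1:**
- Exposure prevalence with Z: odds (0.40/0.60) × 2 = 1.333, so 0.571.
- Cases: 0.30 × 0.571 + 0.70 × 0.40 = 0.451.
- Share of Z among hospital controls: 0.30 × 2 / (0.30 × 2 + 0.70) = 0.462.
- Exposure among hospital controls: 0.462 × 0.571 + 0.538 × 0.40 = 0.479.
- OR = (0.451/0.549) / (0.479/0.521) = 0.895, or about 0.90.

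**Same case, Z acts on a quarter of control injuries.** Here a quarter of the control-injury rate without Z is of the type that Z affects, so the overall rate ratio is 1 + 0.25 × (2 − 1) = 1.25.
- Share of Z: 0.375/1.075 = 0.349.
- Exposure among hospital controls: 0.460.
- OR = 0.967, or about 0.97.

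**Range:**

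| k | Null OR, Z acts on all control injuries | Null OR, Z acts on a quarter | True 0.64 appears as (all) |
|---|---|---|---|
| 1.5 | 0.96 | 0.99 | 0.62 |
| 2 | 0.90 | 0.97 | 0.57 |
| 3 | 0.76 | 0.91 | 0.48 |

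If Z and E are inversely related (Z–E odds ratio 1/k, Z acting on all control injuries), a true 0.64 appears as 0.66, 0.71 and 0.84.

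**Simulation.** This used six million children. Z affects E (odds ratio 0.5) and F, and reaches scalds only through a second variable M. Adjusting for M alone is therefore enough for scalds. The true OR is 0.64.

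| Z–F rate ratio | Community, adjusted for M | Hospital, adjusted for M | Hospital, adjusted for M and Z |
|---|---|---|---|
| 1 | 0.643 | 0.647 | 0.649 |
| 1.5 | 0.639 | 0.691 | 0.657 |
| 2 | 0.643 | 0.707 | 0.646 |
| 3 | 0.638 | 0.748 | 0.650 |

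The scald-sufficient set works for community controls and fails for hospital controls. Adding Z repairs it to within simulation error.

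**Two limiting cases:**
- A cause with the same rate ratio (2) for scalds and for the control injury leaves 0.64 unchanged even when unadjusted.
- A direct effect of E on F gives 0.64/RR: 0.80 for RR 0.8, and 0.51 for RR 1.25. No covariate removes this.

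**The case against.** The strongest reply is that the article does not list the diagram or its covariates. It refers to the falls protocol for more detail on methods, and the cross-reference to the matched analysis may mean the same procedure, not the same list. This stands in part: the final set is unknown. But under either reading, the only procedure the article describes has scalds as its outcome. That is a stated rule, not a detail left out.

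A reader might infer that the hospital-control odds ratios are biased as a matter of fact. The documents do not support that. Age, gender, deprivation and distance are always in the model, and other shared causes may enter through the scald set. No omitted common cause is identified. Housing tenure, overcrowding and long-term health conditions are conceivable candidates, but Table 1 lists them as potential confounders, so they may be included. Their link to kettle, cooker or hot-drink practices is also not shown.

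A reader might also take the bottom row of the first table (k = 3, a null appearing as 0.76) as the likely size. That needs strong associations and a cause that acts on every control injury. The candidates just named would act mainly through one mechanism each, such as staircase falls or poisoning, and the mix of mechanisms is not stated. At an assumed quarter share the same setting gives 0.91.

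Nor does the point undermine the study as a whole. It concerns the additional control group only.

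**Conclusion.** The point holds as a weakness in a stated rule. An adjustment set that is minimal for scalds is not guaranteed to be sufficient when controls are selected by falls or poisoning, so the hospital-control odds ratios can be biased even for exposures without any effect on those injuries. Whether they will be biased, how much and in which direction cannot be told from the article.

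With the assumed inputs and associations of 2, the shift of a null odds ratio is between about 0.97 and 0.90, depending on how many of the control injuries the omitted cause affects. It goes the other way under an inverse relation. The matched community results and the sample size are not affected. This is a cheap improvement to a secondary comparison, not a demonstrated error in the results.

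**What to change.** In the Analysis section, replace the cross-reference to the matched analysis for the hospital-control models with a rule of their own, along these lines: the adjustment set for these models will come from a causal diagram that also contains the control injuries (falls, poisoning) as the basis of control selection. It will be chosen to close both exposure–scald and exposure–control-injury paths, from Table 1 covariates that are not consequences of the injury. The a priori covariates stay.

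The candidate covariates are already measured, so no new data are needed. The diagram work has to cover four control mechanisms. The models gain a few covariates, lose some records to missing data and give slightly wider confidence intervals.

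This does not repair exposures that may themselves affect falls: safety gates, play pens, stationary activity centres and baby walkers. State that their hospital-control odds ratios will be interpreted separately.

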### Sample size

Based on data on the prevalence of exposures and the amount of missing data obtained from analysis of the first 428 controls recruited across all the ongoing case–control studies, 259 cases and 1036 matched controls are required to detect an OR of 0.64 (equivalent to an OR of 1.56 for a risk factor), with 80% power, a 5% significance level, a correlation between matched cases and controls of 0.1 and an average of four controls per case.

### Ethics committee and regulatory approvals

Ethical approval was provided by the Nottingham 1 Ethics Committee (reference number: 09/H0407/14). Approval has been obtained from National Health Service research and development departments providing research governance to participating hospitals and MIUs.

## Discussion

This large, multicentre case–control study will investigate modifiable risk factors for scald injuries in the homes of children under the age of 5 years. The study will attempt to address some of the limitations of previous studies and will use multiple methods to minimise a range of biases. Cases and community controls will be matched on age and gender, and hospital and community controls will be used. A wide range of exposures will be measured, using, where possible, previously validated questions to help minimise misclassification bias. In addition, a concurrent study validating self-reported exposures will enable quantification of under-reporting or over-reporting of exposures by cases and controls.^38^ Further efforts to reduce misclassification bias include restricting measures of exposure to a short time period (maximum of 1 week) prior to the injury for cases, and prior to questionnaire completion for the controls. Data will be collected on a wide range of confounding factors using validated tools wherever possible. The findings from this study should provide evidence to inform scald prevention policy and practice, with implications for child health surveillance programmes and home safety equipment schemes. Our findings should also inform the advice provided during home safety assessments and other child health promotion contacts.
